## Abstract

**Background:**

Atopic dermatitis is a chronic inflammatory skin disease with a high prevalence rate and a large socioeconomic cost. There are many treatments for atopic dermatitis, such as antihistamine, tacrolimus and corticosteroids. However, due to concern about the adverse effects, many patients seek alternative treatments. In this context, natural products are gaining interest. KM110329 is a functional food consisting of four herbs that are beneficial to skin health. The purpose of this study is to assess the efficacy and safety of KM110329 for atopic dermatitis.

**Methods/design:**

This study is a randomised, double-blind, placebo-controlled and multicentre trial of KM110329. For this study, we will recruit 66 atopic dermatitis patients of both sexes, with ages ranging from 18 to 65, from three university hospitals. The participants will receive either KM110329 or a placebo twice a day for 8 weeks. The primary end point will be a change in the scoring atopic dermatitis (SCORAD) index. The secondary end points will include changes to the dermatology life quality index (DLQI) and transepidermal water loss (TEWL), among others. The outcomes will be measured at every visit. The study will be continued for 8 weeks and will include five visits with each subject (at screening and at 0, 1, 4 and 8 weeks).

**Discussion:**

This trial will provide research methodologies for evaluate clinical efficacy and safety of KM110329 in adult patients with atopic dermatitis. In addition, we will evaluate the changes in the general skin health status and quality of life.

**Trial registrations:**

ClinicalTrials.gov NCT01692093.

## Background

Atopic Dermatitis (AD) is a chronic inflammatory pruritic skin disease that is often associated with other atopic disorders, such as allergic rhinitis and asthma [1]. AD is characterised by poorly defined erythema with oedema, vesiculation, weeping in the acute stage, and skin thickening (lichenification) in the chronic stage [2].

The prevalence of AD has risen substantially in many countries in recent decades. AD not only leads to a low quality of life, but it also causes depression. AD affects the patients as well as their parents and other family members as well [3]. Therefore, the socioeconomic cost of AD is increasing. In Korea, the total number of people who visit the hospital for AD is 1,035,680 (57^th^ of total 500 disease), and the total was 62,381,288,330 Won in 2010. In addition to the medical market for AD treatments, there is also an enormous cosmetic market totalling approximately 100 billion Won.

The existing treatments for treat AD include topical corticosteroids, emollients, topical tacrolimus, topical 1% pimecrolimus, oral antihistamines, refined-coal tar, topical doxepin and oral corticosteroids. However, these treatments can cause adverse reactions, such as stinging, burning, drowsiness, itching, dyspepsia and hypertension.

Therefore, a demand for novel treatments exists, and functional foods made from natural products have received considerable attention due to the perception that they have no adverse effects [2].

KM110329 is compound found in Rubi Fructus, Houttuyniae Herba, Rehmanniae Radix, and Betulae Platyphyllae Cortex.

According to herbology textbooks and the World Health Organization (WHO) glossary, the Korean medicinal efficacies of each component of KM110329 are as follows [4,5].

The effects of Rubi Fructus are to tonify the kidney, to secure its essence and to reduce urination. Rubi Fructus works as a treatment for insufficient consolidation due to kidney deficiency, and it also has beneficial effects on the skin.

Houttuyniae Herba has the function of clearing away heat, detoxifying the body, dissolving boils and draining pus. As a home remedy, it is used to treat furuncle.

Rehmanniae Radix clears heat, engenders fluid, cools the blood to stop bleeding and treats agitation, thirst and skin irritation caused by heat.

Betulae Platyphyllae Cortex mitigates pruritus and skin pain by clearing heat, draining dampness, dispelling phlegm and suppressing cough, dispersing swelling, and detoxifying the body.

Some studies have reported the components of KM110329 have effect on atopic dermatitis. Recent studies suggests that Rubi fructus regulates anaphylaxis and have anti-inflammatory effect [6,7]. Rehmanniae Radix prevents skin allergic reaction and treats allergen-induced atopic dermatitis in mice by suppressing the expression of cytokines, chemokines and adhesion molecules [8,9]. Houttuyniae Herba suppresses Th2 immune response and regulates inflammatory process [10,11]. Betulae Platyphyllae Cortex inhibits the development of atopic dermatitis-like skin lesions in NC/Nga mice through the suppression of the Th2 cell response. It also attenuates mast cell-mediated allergic inflammation in vivo and in vitro [12,13].

The aim of the present study is to determine the clinical efficacy and safety of KM110329 for AD.

We will conduct a randomised, double-blind, placebo-controlled, multicentre trial of KM110329 in adult patients with AD. Because of the absence of a gold standard for the treatment of AD, this trial will be conducted to determine the effectiveness of this functional food in comparison with a placebo-controlled group.

## Methods/design

A randomised, double blind, placebo-controlled, multicentre trial will be conducted at the Seoul St. Mary’s Hospital, Chung-ang University Hospital, and Kyung Hee University Hospital in Gangdong. Participants fulfilling the eligibility criteria will be selected. The enrolled participants will be randomly allocated to two parallel groups corresponding to the KM110329 and placebo arms. Each participant will be examined for signs and symptoms of AD before and after taking the functional food. Figure 1 shows the schematic flow of the study.

**Figure 1 F1:**
[figure not shown]
Study flow chart.

### Recruitment

Subjects will be recruited through three routes. Patients who visit the trial hospitals and meet the criteria will be recommended by the physician in charge. Patients who see the trial poster on bulletin boards or advertisements in newspapers will visit the trial site voluntarily.

### Inclusion criteria and exclusion criteria

The inclusion and exclusion criteria are shown in Inclusion and exclusion criteria section.

### Inclusion and exclusion criteria

Inclusion criteria

1. Men and women ages 18 to 65 years

2. Individuals diagnosed with atopic dermatitis according to the criteria of Hanifin and Rajka

3. Individuals with mild to moderate atopic dermatitis (objective SCORAD ≤ 40)

4. Written informed consent for participation in the trial

Exclusion Criteria

1. Severe skin disease other than atopic dermatitis

2. Secondary infection with bacteria, fungi, or virus

3. Uncontrolled hypertension (SBP > 145 mmHg or DBP > 95 mmHg)

4. Severe liver disability (2.5-fold the normal high range value for ALT, AST)

5. Severe renal disability (sCr > 2.0 mg/dl)

6. Women who are pregnant, lactating, planning a pregnancy or women of child-bearing age who do not agree to use proper contraception

7. Use of oral steroids, oral antibiotic or other immunosuppressants within the past 4 weeks

8. Treated by systemic photochemotherapy within the past 4 weeks

9. History of drug abuse

10. Hypersensitivity to Rubi Fructus, Houttuyniae Herba, Rehmanniae Radix, or Betulae Platyphyllae Cortex

11. Use of other investigational products within the past two months

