### Subject withdrawal criteria

1. Use of any forbidden medication or treatment during the trial that could affect the study result

2. Subject’s withdrawal of consent

3. Occurrence of a serious adverse event

4. Detection of eligibility violations, occurrence of other significant protocol violations during the trial

5. Investigator’s decision to terminate the process for the sake of the subject’s health

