### Sample size

Sample size calculations were performed to determine the number of participants needed to detect the effect sizes. We obtained an effect size from the previous study and based on the agreement of experts [14]. The results from the previous study were used to calculate the standard deviation [15]. The mean difference and standard deviation of the scoring atopic dermatitis (SCORAD) index were 10 and 13.576, respectively. The following formula was used to estimate the sample size.

$$\begin{array}{ll} n & =\frac{2{\left(z_{\alpha /2}+z_{\beta }\right)}^{2}\sigma^{2}}{{\left(\mu_{c}-\mu_{t}\right)}^{2}}\\ & =\frac{2\times {\left(1.96+0.84\right)}^{2}\times 13.576^{2}}{10^{2}}\\ & =28.932 \end{array}$$

The calculation was performed using 80% power, a 5% significance level, and a 10% dropout rate. The required sample size is approximately 33 participants for each group. Therefore, a total of 66 participants are needed for this trial.

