### Randomisation and allocation

The study subjects who satisfy the eligibility criteria will be randomised using a computer program at an independent centre (Kyung Hee University Center for Clinical Research and Drug Development; KCRD). Block randomisation with block size of 4 will be performed. The study subjects will be assigned to one of two groups with a 1:1 allocation ratio by investigator in each study site. Random numbers will be sent to each centre, and a randomisation table will be maintained by KCRD during the research period. Opaque sealed envelopes containing serial numbers will be delivered to each centre. The randomisation table kept in an opaque sealed envelope by the contract research organisation (CRO; KCRD) should be opened according to Standard Operating Procedures (SOPs).

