### Treatment protocol

The participants will receive KM110329 or a placebo drug for eight weeks. They will take 2 tablets by mouth with water twice a day after meals.

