### Interventions

Hanpoong Pharm and Foods Co., Ltd. produced the KM110329 and the placebo according to Korea Good Manufacturing Practice (KGMP) standards. KM110329 is a brown-coloured, round-shaped tablet. It is compound of Rubi Fructus, Houttuyniae Herba, Rehmanniae Radix, and Betulae Platyphyllae Cortex. The placebo medicine is made of lactose, corn starch and food colouring, and it has a similar appearance, shape, weight, taste and colour as KM110329.

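### Exclusion 10 covers hypersensitivity to the four herbs only, so a person with a known reaction to a stated placebo ingredient is eligible for randomisation

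*Protocol article*

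**What the plan says.** The protocol article prints a numbered list of 4 inclusion and 11 exclusion criteria (Inclusion and exclusion criteria) and does not describe it as a selection. Exclusion 10 is the only item on hypersensitivity: "Hypersensitivity to Rubi Fructus, Houttuyniae Herba, Rehmanniae Radix, or Betulae Platyphyllae Cortex". It names four substances and has no closing phrase to bring in other ingredients.

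Interventions describes both products. Of KM110329 it says: "It is compound of Rubi Fructus, Houttuyniae Herba, Rehmanniae Radix, and Betulae Platyphyllae Cortex". It gives no excipients for that tablet. Of the comparator it says: "The placebo medicine is made of lactose, corn starch and food colouring".

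Under Randomisation and allocation, participants are "assigned to one of two groups with a 1:1 allocation ratio". Treatment lasts eight weeks, and Treatment protocol says: "They will take 2 tablets by mouth with water twice a day after meals".

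The nearest other safeguard is under Subject withdrawal criteria: "Investigator’s decision to terminate the process for the sake of the subject’s health". It applies once a person is in the trial.

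**The concern.** Everyone enrolled may receive either product, so a hypersensitivity criterion would be expected to cover both. Exclusion 10 accepts that people known to react to a product should not be given it, but applies this only to the named active ingredients.

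Two things are at stake. The first is participant safety: a known reactor could be given an ingredient that a single screening question would have identified. The second is how adverse events are read: reactions to an inactive ingredient would enter the tables of a trial whose stated aims include safety, although they say nothing about KM110329.

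**Working it through.** **Step 1. Compare the criteria with the products.**

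| Ingredient | Product in which it is stated (Interventions) | Covered by exclusion 10? | Covered by another entry criterion? |
|---|---|---|---|
| Four herbs | KM110329 | Yes | Not needed |
| Lactose | Placebo | No | No |
| Corn starch | Placebo | No | No |
| Colouring | Placebo | No | No |
| Excipients of KM110329 | Not stated | No | No |

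The other ten exclusions concern skin disease and infection, blood pressure, liver and renal function, pregnancy and contraception, recent systemic treatment or photochemotherapy, drug abuse, and other investigational products. None concerns allergy, intolerance or excipients, and the list has no exclusion at the investigator's discretion.

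**Step 2. Chance of exposure.** With 1:1 allocation, an eligible person with such a hypersensitivity receives placebo with probability 1/(1+1) = 0.5. If the KM110329 tablet contains the same ingredient, the chance of exposure is higher, up to 1.

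**Step 3. Plan's own figure, for context.** The Sample size section gives: "The mean difference and standard deviation of the scoring atopic dermatitis (SCORAD) index were 10 and 13.576, respectively". The printed formula yields 2 × (1.96 + 0.84)² × 13.576² / 10² = 28.90. The article prints 28.932, a rounding difference. Rounded up this is 29 per group, and 29/(1 − 0.10) = 32.2, so 33 per group and 66 in total. The plan's figure reproduces, and the present point does not change it.

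**Step 4. Scale under assumed inputs.** The article gives no rate of reactions to the placebo ingredients and no size of worsening. Assume that a share p of participants reacts, with p = 1%, 3% or 5%, and that each reactor on placebo worsens by 10 SCORAD points. Both inputs are illustrative.

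| p | Expected reactors among 33 on placebo, 33p | Chance of at least one, 1 − (1 − p)³³ | Shift in placebo mean, 10p |
|---|---|---|---|
| 1% | 0.33 | 28% | 0.1 points |
| 3% | 0.99 | 63% | 0.3 points |
| 5% | 1.65 | 82% | 0.5 points |

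One reactor with an adverse event adds 1/33 = 3 percentage points to the placebo event rate.

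Taking the planning SD as the SD of the change score, the standard error of the difference between groups is 13.576 × √(2/33) = 3.34 points. The shift is then 0.1/3.34 = 0.03 to 0.5/3.34 = 0.15 of a standard error, or 1% to 5% of the planned 10-point difference.

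These figures count everyone who reacts. A wider exclusion removes only people who already know that they react, so what it would prevent is at most this and could be much less.

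**The case against.** A reader might infer that the gap biases the trial in favour of KM110329, because herb reactors are screened out and placebo reactors are not. The article does not support that. The inference needs lactose, corn starch and colouring to be absent from the active tablet, and the excipients of that tablet are not given. If the tablets share ingredients, the gap applies in both groups and any directional effect shrinks or disappears. This objection stands.

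A reader might also infer a threat to the efficacy result, or take the 28% to 82% range as the chance of harm. Neither follows. The SCORAD shift is small even under the assumed inputs, and the percentages give the chance that at least one reactor of any kind is in the placebo group. They do not give the chance of an adverse event or of a preventable one. This stands as well.

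The Background describes atopic dermatitis as "often associated with other atopic disorders, such as allergic rhinitis and asthma". That names rhinitis and asthma; nothing in the article links the condition to reactions to these ingredients, so it adds little.

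Exposure need not last the full eight weeks. Table 1 schedules adverse event checks at days 7, 28 and 56, and participants can be discontinued for a serious adverse event, by the investigator's decision or by withdrawing consent. Medical history is also taken at every visit, including screening. These provisions limit the consequence without closing the gap: they act after the first dose, or they depend on judgement with no criterion behind them.

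Finally, the two sections do not contradict each other, and the article condenses a full protocol that is not shown and may word the criterion more broadly. That is possible. But the article does state a hypersensitivity criterion, in closed wording, and does state the placebo composition. The point is therefore that a stated criterion is too narrow for the products described, not that detail is missing.

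**Conclusion.** The point holds as a minor, avoidable participant-safety gap. Under the printed criteria, a person with a known hypersensitivity to a stated placebo ingredient is eligible and has about a 50% chance of being allocated to placebo. Some adverse events unrelated to KM110329 could result.

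How many participants would be affected cannot be computed from the article, and the direction and size of any bias cannot be established. No material effect on the primary SCORAD comparison is shown, and sample size, significance level and the primary test are untouched. The conclusion assumes that the printed list is the operative one; if the full protocol already has broader wording, the sponsor can settle the matter by confirming it.

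**What to change.** Reconcile exclusion 10 with the composition given under Interventions, so that it covers known hypersensitivity to any ingredient of either study product, KM110329 or placebo, and apply it to every candidate before randomisation. This works whether or not the two tablets share excipients.

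The cost is a few words in the criterion and one question at screening. The downside is that a few candidates may be screened out.

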### Subject withdrawal criteria

The subjects who meet the criteria listed in Subject withdrawal criteria section will be discontinued from treatment. The participants who are withdrawn after randomisation will be followed for outcomes.

### Subject withdrawal criteria

1. Use of any forbidden medication or treatment during the trial that could affect the study result

2. Subject’s withdrawal of consent

3. Occurrence of a serious adverse event

4. Detection of eligibility violations, occurrence of other significant protocol violations during the trial

5. Investigator’s decision to terminate the process for the sake of the subject’s health

### Sample size

Sample size calculations were performed to determine the number of participants needed to detect the effect sizes. We obtained an effect size from the previous study and based on the agreement of experts [14]. The results from the previous study were used to calculate the standard deviation [15]. The mean difference and standard deviation of the scoring atopic dermatitis (SCORAD) index were 10 and 13.576, respectively. The following formula was used to estimate the sample size.

$$\begin{array}{ll} n & =\frac{2{\left(z_{\alpha /2}+z_{\beta }\right)}^{2}\sigma^{2}}{{\left(\mu_{c}-\mu_{t}\right)}^{2}}\\ & =\frac{2\times {\left(1.96+0.84\right)}^{2}\times 13.576^{2}}{10^{2}}\\ & =28.932 \end{array}$$

The calculation was performed using 80% power, a 5% significance level, and a 10% dropout rate. The required sample size is approximately 33 participants for each group. Therefore, a total of 66 participants are needed for this trial.

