### Primary outcome measurement

The primary outcome in the present study is the change in the SCORAD index between the baseline (Visit 2) and after the treatment (Visit 5). The SCORAD index is a clinical tool for assessing the severity of atopic dermatitis as objectively as possible. The SCORAD index will be measured at every visit.

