### Statistical analysis

#### Efficacy assessment

Statistical analyses will be performed for both the ITT (intention-to treat, all randomly assigned participants) and PP (per-protocol, participants completed the trial without any protocol deviations) data sets. The missing values will be imputed by the last observation carried forward (LOCF) method. The continuous variables will be displayed as the mean ± SD(standard deviation), and the categorical variables will be displayed as the n (%). The baseline characteristics will be compared by either a Student’s *t*-test for continuous variables or the χ^2^ test (Fisher’s exact test will be used when the expected value is < 5) for the categorical data. Alternatively, McNemar’s test will be used if the normality assumption is not satisfied for the continuous variables. For the primary outcome measures, the mean differences from the baseline values to the end of treatment will be compared using an independent T-test.

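### The sample size uses an SD worded as that of the SCORAD index, but the primary test is an unadjusted t-test on change. If 13.576 is the SD of the score, 80% power needs a baseline-to-week-8 correlation of about 0.45 to 0.50 or more; adjusting for baseline largely removes that condition

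*Protocol article*

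**What the plan says.** All references are to the protocol article.

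- **Sample size.** The formula is the one for two independent means. Its inputs are given as: "The mean difference and standard deviation of the scoring atopic dermatitis (SCORAD) index were 10 and 13.576, respectively". On where the SD comes from, the section says: "The results from the previous study were used to calculate the standard deviation". The design values are "80% power, a 5% significance level, and a 10% dropout rate". The result is 28.932 per group before dropout, 33 per group after it, and 66 in total.
- **Primary outcome measurement.** The outcome is a change score: "the change in the SCORAD index between the baseline (Visit 2) and after the treatment (Visit 5".
- **Statistical analysis, Efficacy assessment.** For the primary outcome, "the mean differences from the baseline values to the end of treatment will be compared using an independent T-test". No baseline covariate is mentioned. The same section plans ITT and per-protocol analyses, with missing values filled by LOCF.
- **Randomisation and allocation.** Participants are "assigned to one of two groups with a 1:1 allocation ratio".

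The article does not say whether 13.576 describes a single-visit score or a change, or which visit it belongs to. It gives no correlation between baseline and week 8.

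**The concern.** The power of a t-test on change depends on the SD of change. Taken as worded, the sample-size input is the SD of the index itself. With equal SDs at the two visits, these are the same number only when the baseline-to-week-8 correlation is 0.5. Below that, change scores vary more than the scores and the planned test has less power than stated; above it, the test has more.

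What is at stake is whether the 80% quoted for the primary comparison belongs to the test that will be run. The difference of 10 and the SD are also credited to different sources (one study plus expert agreement for the first, another study for the second), so they need not describe the same quantity.

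**Working it through.** **Inputs from the protocol article:** difference 10 and SD 13.576; two-sided 5% level (1.96 in the formula); 80% power (0.84); 10% dropout; 33 per group; 1:1 allocation.

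**Assumptions, not in the documents:** rho from 0.2 to 0.7, and equal SDs at baseline and week 8 unless stated otherwise.

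**Step 1. Reproduce the stated size.** 2 × (1.96 + 0.84)² × 13.576² / 10² = 28.90, or 28.93 with unrounded z values, which is the printed figure. Rounded up this is 29, and 29 / 0.9 = 32.2, so 33 per group and 66 in total. The arithmetic is correct.

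**Step 2. Number analysed.** 33 × 0.9 = 29.7 per arm if dropouts are lost. Up to 33 per arm enter an ITT analysis with LOCF.

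**Step 3. If 13.576 is the SD of the score.** The SD of change is 13.576 × √(2(1 − rho)). For example, at rho 0.3 it is 13.576 × √1.4 = 16.06. The ANCOVA residual SD is 13.576 × √(1 − rho²), taking 13.576 as the week-8 SD. At rho 0.3 that is 13.576 × √0.91 = 12.95. Power for a difference of 10, from the noncentral t distribution:

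| rho | SD of change | t-test, 29.7 per arm | t-test, 33 per arm | ANCOVA SD | ANCOVA, 29.7 per arm |
|---|---|---|---|---|---|
| 0.2 | 17.17 | 0.597 | 0.644 | 13.30 | 0.813 |
| 0.3 | 16.06 | 0.655 | 0.702 | 12.95 | 0.833 |
| 0.4 | 14.87 | 0.722 | 0.767 | 12.44 | 0.861 |
| 0.5 | 13.58 | 0.797 | 0.838 | 11.76 | 0.897 |
| 0.6 | 12.14 | 0.877 | 0.909 | 10.86 | 0.937 |
| 0.7 | 10.52 | 0.950 | 0.967 | 9.70 | 0.974 |

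The correlation at which the t-test reaches 80% is 0.504 at 29.7 per arm and 0.447 at 33 per arm. The second figure assumes that LOCF does not shrink the difference of 10.

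To show the scale in participants: at rho 0.3 the t-test on change would need 2 × 2.80² × 16.06² / 100 = 40.4, so 41 per group. After dropout that is 41 / 0.9 = 45.6, so 46, against the 33 planned.

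**Step 4. ANCOVA at rho = 0.** The residual SD is then 13.576 itself and power at 29.7 per arm is 0.797. That is the same figure the t-test gives with the protocol's own inputs, so with a week-8 SD of 13.576 ANCOVA power is about 80% or more at any rho.

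**Step 5. If 13.576 is already the SD of change.** The planned t-test has power 0.797 at 29.7 per arm and 0.838 at 33. No condition on rho applies.

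**The case against.** The strongest objection is that the premise cannot be proved. The study behind the SD is not shown, and the wording is loose: the SD is quoted in one breath with a mean difference, and the analysis section uses nearly the same term for change from baseline. The figure may well be an SD of change. This stands. A reader might infer that the trial is underpowered or that its stated power is wrong, and the documents support neither. Nothing in them shows that SCORAD at visits eight weeks apart correlates below 0.5, and at higher correlations the trial has more power than stated.

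The threshold of 0.5 is also not fixed. It falls to about 0.45 if all 33 per arm are analysed, and it depends on equal SDs at both visits. Entry is capped at an objective SCORAD of 40, so the baseline spread could be narrower. If 13.576 were the week-8 SD and the baseline SD were 0.8 of it (an assumption), the SD of change would equal 13.576 at rho = 0.8 / 2 = 0.40. This stands too.

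Nor does ANCOVA guarantee 80% under every reading. Suppose 13.576 is a baseline SD and the week-8 SD is 20% larger (an assumption), that is 1.2 × 13.576 = 16.29. ANCOVA power at 29.7 per arm is then 68% at rho 0.3 (residual SD 15.54) and 77% at rho 0.5 (residual SD 14.11). A claim that ANCOVA secures the stated power whatever 13.576 means would go too far.

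Finally, a t-test on change is a valid analysis, and where an SD came from is a detail that a condensed article may leave out. Both points are fair, and a bare request for the source would be only a request for detail. What remains is that the article itself fixes the input, the endpoint and the test. The first, as worded, does not match the other two, and a more precise analysis is available from data already collected.

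**Conclusion.** The point holds in conditional form. The sample-size arithmetic is right. The input is labelled as the SD of the index while the primary test is on change, and nothing in the article connects the two.

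- If 13.576 is the SD of the score, with equal SDs at both visits, the t-test has about 60% to 95% power over rho 0.2 to 0.7 at 29.7 per arm, and 64% to 97% at 33 per arm. The stated 80% needs rho of about 0.45 to 0.50 or more.
- If 13.576 is the SD of change, the stated power stands at about 80% and only the label is wrong.

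The case for adjusting for baseline does not depend on which reading is true. In large samples ANCOVA is never less precise than the t-test on change, at the cost of one degree of freedom. The range of rho is an assumption throughout.

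**What to change.** 1. In the Efficacy assessment section, make the primary analysis an ANCOVA of Visit 5 SCORAD (or its change from Visit 2) on treatment, with Visit 2 SCORAD as covariate. Both forms give the same treatment estimate. With a week-8 SD of 13.576 this gives 81% to 97% power over rho 0.2 to 0.7 at 29.7 per arm, and about 80% at rho 0.
2. In the Sample size section, say whether 13.576 is the SD of a score or of change and, if of a score, at which visit.
3. If it is the SD of a score, restate the power of the planned test over a range of rho such as 0.3 to 0.7, with the assumption made about the SD at the other visit.

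The cost is one sentence changed in the analysis section and one paragraph restated in the sample-size section. The change of primary analysis should be made before unblinding. It needs no new measurements, because SCORAD is already scheduled at Visit 2, and no more participants.
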